## Abstract

**Introduction:**

In today’s military landscape, optimizing performance and bolstering physical health and mental resilience are critical objectives. Introducing a 12-week Ashtanga Vinyasa Yoga Supta Method (AVYSM) to the training protocol of military trained Airforce pilots, we aim to assesses the feasibility and impact of the method.

**Materials and equipment:**

Borg Scale assesses the intensity level of physical activity during the intervention. Flight simulator data gauges operational performance responses. Postural control responses are measured using a force platform, stress responses are monitored via heart monitor, and handgrip dynamometry will measure strength. Respiratory capacity is assessed using a spirometer, body composition is evaluated using impedance balance, and aviation-related questionnaires are administered before and after the intervention period.

**Methods:**

In a randomized controlled trial, the totality of pilots from the “Masters in Military Aeronautics: aviator pilot specialist” course at the Portuguese Air Force Academy (PAA) were randomly assigned to the yoga intervention or the waiting list control groups, with participants providing written informed consent. The control group followed protocolized course classes for 12 weeks, while the intervention group integrated two weekly one-hour yoga sessions into their course.

**Results:**

The PAA has approved the implementation of this intervention protocol at Airbase 11 in Beja, highlighting its significance for the organization’s policy makers. We hypothesize that this method will enhance operational performance and, subsequently, elevate flight safety.

**Discussion:**

This research’s potential extends beyond the PAA, as it can be adapted for use in Airforce departments of other nations and various military contexts.

**Clinical trial registration:**

Évora University research ethics committee—approval number 21050. Study registered on ClinicalTrials.gov under identifier NCT05821270, registered on April 19, 2023.

## Introduction

1

Air Force pilots, being healthy adults in a specialized profession, need specific training to maintain optimal performance and safety in the challenging conditions of aviation (1). This profession can negatively affect their performance, physical, and mental well-being, due to:Exposure to environmental elements includes factors such as noise, vibration, psychophysiological fatigue, and spatial disorientation (1).The evolution of aircraft design has brought about notable improvements in engine performance and aerodynamics, enabling pilots to navigate at elevated altitudes and contend with increased gravitational forces (G-forces). These advancements significantly amplify pilots’ psychophysiological responses, especially when combined with the effects of hypoxia, thereby markedly influencing the visual and auditory reaction times of the crew (1, 2).Hypoxia stands as the primary hazard during high-altitude flights, leading to increased perceived stress and exertion, elevated heart rate, and reduced functionality of respiratory muscles. Exposure to hypoxia can impair working memory and pattern recognition, posing significant challenges to pilots (3).Elevated physiological responses to task-related or cognitive stressors can hinder the ability to navigate and address stressful situations effectively (4).Demands of piloting a military aircraft include the efficient operation of the vestibular system to maintain balance within the aircraft cabin (5). Fighter pilots often show a heightened susceptibility to spatial disorientation, which can be attributed to the unique characteristics of the aircraft they pilot. Each aircraft is designed for specific functions, contributing to individual variations in susceptibility (6). An essential attribute of the postural control system is its capacity to devalue unreliable sensory information while prioritizing more dependable inputs—commonly referred to as sensory recalibration. This ability implies that, when confronted with visual impairments, reliance on alternative sensory information systems may be intensified. However, this heightened reliance requires specific training. Targeted balance training has shown promise in significantly improving postural stability by strengthening or recalibrating the remaining sensory systems (7).

Understanding these modern military demands can provide insights for specific training to better prepare pilots and aircrews in countering these threats. Recognizing these factors opens new avenues for training and cognitive preparation (3, 4).

Among various exercise options, incorporating yoga into pilot training is a practical choice for the pilots’ demands: its multisensory approach engages compensatory sensory systems in the vestibular system that improve balance, stability, and coordination, while also addressing aspects such as breathing to develop the respiratory system, physical postures to enhance flexibility and strength, embodiment for increased proprioception, and meditation for cognitive preparation (7–11). This method not only addresses the distinctive challenges encountered by pilots but also the expected enhancements in overall well-being and cognitive performance are poised to positively impact decision-making processes and operational performance during aircraft operations (4).

Yoga encompasses physical, mental, and spiritual practices originating from India. Ashtanga Vinyasa Yoga, known for its substantial movement and complex postures, is a physically demanding style of yoga. It involves interconnected physical postures (asanas), flowing movements (vinyasas), and synchronized breathing techniques (pranayama). Ashtanga emphasizes the harmony of posture, breath control, and gaze. It requires a focus on physical embodiment, coordinating each movement with inhalation or exhalation, which makes it a form of “moving meditation” (8, 9). Various yoga modalities have been shown to have predominantly positive outcomes in different populations (10). The viniyoga principle emphasizes ongoing adaptation for therapeutic benefits, covering poses, conscious breathing, meditation, and philosophy, allowing practitioners to tailor their practice to their health, age, occupation, and lifestyle (11).

In line with this methodology, a specialized yoga practice, AVYSM, tailored for Air Force Pilots has been developed. Understanding the previously mentioned challenges and responsibilities faced by Airforce pilots will be instrumental in guiding the development and evaluation of strategies and training programs, especially:establishing the efficacy of AVYSM in refining stress responses in individuals, thus improving cognitive response, and decision-making.scrutinizing the impact of AVYSM in stimulating the recalibration of the vestibular system, above all during rotational tasks implying changes in head position in space, to augment postural stability and balance, thereby mitigating spatial disorientation.evaluating the extent to which AVYSM contributes to enhanced overall health, body composition, strength, and respiratory performance, serving as a potential countermeasure against hypoxia threats and increased G-forces in the aircraft.

This study aims to determine the suitability of incorporating this method into the training program for Portuguese Air Force pilots, with the goal of enhancing their capabilities and increasing flight safety by preventing human error.

## Materials and equipment

2

Material and equipment selection for the study prioritized availability, capability to measure physiological functions impacted by piloting military aircraft, suitability for real-life training integration, and efficiency in delivering results without hindrance to pilots’ daily workload, as well as adherence to the highly specific military regulations in force.

Both primary and secondary outcomes were selected following a comprehensive review of the literature and a comparison with pilots’ perceived difficulties (as identified through a brief interview, detailed in the study flow). Primary outcomes were deemed the most critical factors in flights, with Operative Performance being the most crucial for pilots’ safety. Secondary outcomes were also identified as significant contributors.

### Primary outcomes

2.1

Changes in Operative performance—Flight times to complete tasks in the flight simulator; number of errors during the emergency protocol and their classification report from the flight simulator controller (12). The assessment will determine if the exercise protocol influences the pilot’s decision-making, as evidenced by improved task efficiency, reduced errors, and enhanced visual and auditory reaction times (1, 2)—Time Frame: measured at 12 weeks (vs. baseline values).

Changes in Stress and HRV—Heart rate variability, measured with Polar H10 portable device (2, 13–15). The assessment will reveal if the exercise protocol influences pilots’ responses to stressors, with a lower stress response enhancing decision-making (4)—Time Frame: measured at 12 weeks (vs. baseline values).

Changes in Vestibular system control responses—The Center of Pressure (CoP) represents the dynamics of the neuromusculoskeletal system, was measured with a portable force plate (Biosignals Plux-Portugal) with a sample frequency at 1000 hz. and data downsampled to 100 Hz (16, 17). Preprocessing performed using the EEGLAB toolbox, which is available for use in MATLAB (The MathWorks Inc., Natick, MA) (18). Enhanced postural control responses may indicate the protocol’s potential to mitigate the effects of spatial disorientation (6, 7)—Time Frame: measured at 12 weeks (vs. baseline values).

### Secondary outcomes

2.2

Changes in Strength—Handgrip strength measured with a handgrip dynamometer Baseline Smedley, Model 12–0286, White Plains, NY, United States (19). The assessment will determine if the exercise protocol impacts pilot strength, crucial for maintaining control, resisting fatigue, and ensuring safety during high-intensity flights (2)—Time Frame: measured at 12 weeks (vs. baseline values).

Changes in Body composition—Body composition data (percent body fat, percent fat free mass, percent muscle mass index, as a percentages) measured with a Tanita (MC-780 MA, Tanita, Tokyo, Japan) to get a bioelectrical impedance analysis (BIA) will indicate if the exercise protocol had any impact in the pilot’s physical makeup. Percent body fat, percent fat-free mass, and percent muscle mass index collectively constitute body composition measures. Percent body fat reflects the fat proportion in total body weight, encompassing essential and storage fat. In contrast, percent fat-free mass represents the non-fat components, including muscle, bone, organs, and other tissues. Percent muscle mass index specifically gauges the proportion of body weight attributed to muscle. The relationship between percent body fat and percent fat-free mass is complementary, totaling 100%, while percent muscle mass index indicates the proportion of muscle within total body weight (20, 21). Enhanced body composition could mitigate adverse effects of the pilot profession on physical well-being (1)—Time Frame: measured at 12 weeks (vs. baseline values).

Changes in well-being and general health—measured through the SF-36 V1 questionnaire (22, 23) will indicate if the exercise protocol had any impact in the pilot’s general health subjective assessment, mitigating adverse effects of their profession on pilots’ physical well-being (1)—Time Frame: measured at 12 weeks (vs. baseline values).

Changes in Lung capacity—Ventilatory response measured with spirometry—FEV1/FVC (Forced Expiratory Volume in 1 s and Forced Vital Capacity) ratio indicates how much air you can forcefully exhale (2, 5) will indicate if the exercise protocol had any impact on lung capacity, which might offset hypoxia threats on pilots (3) – Time Frame: measured at 12 weeks (vs. baseline values).

Five Facet Mindfulness Questionnaire (FFMQ)—Changes in cognitive abilities with 15 questions and average scores are calculated by summing the responses and dividing by the number of items, and indicate the average level of agreement with each subscale (1 = rarely true, 5 = always true). Higher scores are indicative of someone who is more mindful in their everyday life (24, 25). Determining the impact of the exercise protocol on cognitive abilities, a more mindful pilot is anticipated to exhibit improved decision-making skills during work (1, 3)—Time Frame: measured at 12 weeks (vs. baseline values).

Multidimensional Assessment of Interoceptive Awareness Questionnaire (MAIA)—Changes in cognitive abilities—is an 8-scale state–trait questionnaire with 32 items to measure multiple dimensions of interoception; scores are between 0 and 5, where higher score equates to more awareness of bodily sensation (26). The evaluation will assess the exercise protocol’s impact on cognitive abilities, expecting improved decision-making in pilots with heightened awareness of bodily sensations (1, 3)—Time Frame: measured at 12 weeks (vs. baseline values).

Aviation Safety Attitude Scale (ASAS)—Changes in cognitive abilities—consists of 27 items on a five-point scale, each designed specifically to assess pilots’ attitudes with respect to predict the hazardous event involvement of aviators; For all the attitude subscales, higher scores indicate a greater degree of that particular attitude—For example, higher scores on the ASAS self-confidence factor indicated that the person expressed greater confidence in their ability as a pilot (27). The evaluation will assess the exercise protocol’s impact on cognitive abilities, anticipating enhanced decision-making skills in more confident pilots (1, 3)—Time Frame: measured at 12 weeks (vs. baseline values).

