#### Sample size determination

3.2.1

Among all military personnel in the Portuguese Air Force, the inclusion criteria for participation in this study comprise healthy individuals serving as military pilots actively engaged in their training (tirocinium) at the PAA, which consists of taking the course titled “Masters in Military Aeronautics: Aviator Pilot Specialist.”

Conversely, the exclusion criteria encompass military pilots on active duty either preceding (not aviation pilots yet) or following the tirocinium (distributed by different airbases inside and outside the country and flying different types of aircrafts in restricted, classified or warzones), those with injuries, and individuals undergoing sudden lifestyle changes (e.g., initiating or discontinuing smoking habits, commencing, or ceasing any form of medication, or adopting a new diet).

There are currently 19 pilots actively undergoing their training (tirocinium) at the PAA, serving within “Esquadra 101 - RONCOS,” situated at Airbase 11 in Beja, which comprises the totality of this population for the PA. These pilots are divided into two classes, and they share common aircrafts, specifically the Aerospatiale Epsilon TB-30. Additionally, both classes are assigned comparable workloads and operational tasks.

Within these criteria there are 19 individuals serving as military pilots actively engaged in their training (tirocinium) at the PAA, specifically within the PA course titled “Masters in Military Aeronautics: Aviator Pilot Specialist,” and our sample size is calculated with OpenEpi, with a 95% confidence interval, which corresponds to 19 subjects—the totality of this population, as seen in Image 1.

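### The lung-capacity outcome is defined by the FEV1/FVC ratio, which is not an amount of air and may miss or reverse a gain in lung volume

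*Protocol article*

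**What the plan says.** The entry in section 2.2 (Secondary outcomes) of the protocol article opens "Changes in Lung capacity—Ventilatory response measured with spirometry". The one spirometric variable it names is FEV1/FVC, of which it says that the "ratio indicates how much air you can forcefully exhale". The bracket after the variable only spells out the two abbreviations. The entry then states the inference to be drawn, that the measure "will indicate if the exercise protocol had any impact on lung capacity, which might offset hypoxia threats on pilots", with change assessed at 12 weeks against baseline.

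Two other places give context but do not repeat the error. The abstract says "Respiratory capacity is assessed using a spirometer" and names no variable. The Introduction lists among the study's purposes "enhanced overall health, body composition, strength, and respiratory performance, serving as a potential countermeasure against hypoxia threats". No section names FEV1 or FVC, in litres or in any other unit, as an outcome in its own right.

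**The concern.** The outcome's name, its variable and its interpretation do not agree. The name and the interpretation concern capacity, which is a volume. The variable is one volume divided by another, so it has no unit and says nothing about how large either volume is. The sentence that joins the two describes FVC, which is the denominator of the ratio and not the ratio.

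At stake is the trial's respiratory question. Breathwork is part of every class, and the stated hope is that greater capacity may help against hypoxia. The participants are healthy trainee pilots, so relief of airflow obstruction, on which the ratio does bear, is not the stated target. If volumes rise, the reported outcome could stay flat or fall. If they drop, it could rise.

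**Working it through.** **Inputs.** From Secondary outcomes: the variable is R = FEV1/FVC, with FEV1 the volume forcibly exhaled in one second and FVC the forced vital capacity. The article gives no baseline or expected volumes, so every litre value below is an assumption for illustration. The article also states no figure for this outcome, so there is nothing of its own to reproduce.

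**Step 1: is the ratio an amount of air?** Three assumed pilots:

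- 2.4 L / 3.0 L = 0.80
- 4.0 L / 5.0 L = 0.80
- 4.8 L / 6.0 L = 0.80

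The third exhales twice the volume of the first (6.0 / 3.0 = 2), yet all three have the same value. The ratio does not show how much air is exhaled.

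**Step 2: how does the ratio respond to change?** Let FEV1 change by fraction a and FVC by fraction b. Then

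new ratio = FEV1(1+a) / [FVC(1+b)] = R(1+a)/(1+b).

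The direction depends only on a and b, whatever the baseline: unchanged if a = b, lower if b > a, higher if a > b.

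**Step 3: illustration from an assumed 4.2 L and 5.0 L, R = 0.84.**

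| Change in FEV1 | Change in FVC | New volumes (L) | New ratio | What the ratio shows |
|---|---|---|---|---|
| +10% | +10% | 4.62 / 5.50 | 0.84 | no change, though both volumes rose |
| +5% | +10% | 4.41 / 5.50 | 0.80 | a fall, though both volumes rose |
| +5% | +2% | 4.41 / 5.10 | 0.86 | a rise, in line with the volumes |
| −5% | −10% | 3.99 / 4.50 | 0.89 | a rise, though both volumes fell |

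The relative changes in the last three rows do not depend on the assumed baseline: 1.05/1.10 = 0.955, 1.05/1.02 = 1.029 and 0.95/0.90 = 1.056.

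**Step 4: the same cases on the volumes.** In the first two rows FVC goes from 5.00 to 5.50 L and in the third to 5.10 L, and each shows as a gain. In the fourth it goes to 4.50 L and shows as a loss. FVC has the right sign in all four rows. The ratio has it only in the third.

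**The case against.** The strongest reply has four parts.

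- **The ratio is not blind to every gain.** It rises whenever FEV1 gains proportionally more than FVC, and the article gives no expected pattern of change. This stands. A reader might infer that the ratio cannot detect a benefit, or that a real benefit would be reported as null or as harm. The documents do not support either statement: the outcome depends on the relative size of a and b, which is unknown.
- **No favourable direction is set.** The entry asks whether there is any impact, and the Statistical analysis section states no sidedness, so a significant fall would still count as an impact. This stands in part. A fall need not be labelled a deterioration. But an effect with the wrong sign does not tell the reader whether capacity rose, and equal proportional gains would still show nothing.
- **The article may condense a fuller spirometry plan.** Both volumes have to be recorded to form the ratio, so it would be wrong to infer that the respiratory question can never be answered from the data. That stands. It does not rescue the entry, because the point is not a missing detail: the article itself fixes the variable and misdescribes it. Reading the slash as a list of two measures does not work either, since the text calls it a ratio.
- **The reach is small.** This is one of seven secondary outcomes, and the Materials and equipment section ranks operative performance as most crucial. That stands and limits the weight of the point.

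**Conclusion.** The point holds in this form: the description of the ratio is wrong, and the ratio is an unreliable index of change in lung volume. It may miss a gain or reverse its sign, and so does not support the stated inference about lung capacity.

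The misdescription needs no assumption. It follows from the article's own expansion of the abbreviations. The rule for when the ratio stays, falls or rises also holds for any baseline. The sizes in litres and the ratio values from 0.80 to 0.89 are illustrations from assumed volumes. Which pattern would occur in these pilots cannot be told from the document.

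Two further inferences should not be drawn. The primary conclusions are not affected, because no primary outcome uses spirometry. Nor does the document show that FVC would settle the hypoxia question. It says only that capacity might offset that threat, and FVC is preferable here simply because it measures the volume that the outcome is named for. The correction should be made, but its importance is that of one secondary outcome.

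**What to change.** In section 2.2, name FVC in litres as the lung-capacity outcome, with FEV1 in litres reported alongside. Keep FEV1/FVC as a descriptive index of airflow, and describe it as the share of forced vital capacity expelled in the first second. How the outcome is compared belongs to the Statistical analysis section and is a separate matter.

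There is no measurement cost: both volumes are needed to form the ratio, so no extra test or participant time is required. There is a procedural cost. The trial is registered and ethics-approved, so a changed outcome variable needs a dated, documented amendment and a matching update wherever the outcome is registered. The registry record is not at hand, so its wording could not be compared.

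The article mixes tenses: the abstract reports randomisation as done and the force-plate measure is described in the past, while other sections look ahead. Data collection may therefore have begun. If any spirometry data were seen before the change, the amendment and the report should say so.

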## Methods

3

### Study design, ethics approval and informed consent publication

3.1

The study was approved by the Évora University Research Ethics Committee, with approval number 21050, and participants gave written informed consent. The study is in agreement with the Declaration of Helsinki. The trial was registered in ClinicalTrials.gov with identifier NCT05821270, registered on 19th April 2023. Furthermore, this intervention protocol was accepted by the PAto be applied on Airbase 11 in Beja. A randomized, prospective, controlled two-arm trial will be adopted, in which one arm will be the control group (waiting list) and the other the intervention group (yoga).

### Participants

3.2

#### Sample size determination

3.2.1

Among all military personnel in the Portuguese Air Force, the inclusion criteria for participation in this study comprise healthy individuals serving as military pilots actively engaged in their training (tirocinium) at the PAA, which consists of taking the course titled “Masters in Military Aeronautics: Aviator Pilot Specialist.”

Conversely, the exclusion criteria encompass military pilots on active duty either preceding (not aviation pilots yet) or following the tirocinium (distributed by different airbases inside and outside the country and flying different types of aircrafts in restricted, classified or warzones), those with injuries, and individuals undergoing sudden lifestyle changes (e.g., initiating or discontinuing smoking habits, commencing, or ceasing any form of medication, or adopting a new diet).

There are currently 19 pilots actively undergoing their training (tirocinium) at the PAA, serving within “Esquadra 101 - RONCOS,” situated at Airbase 11 in Beja, which comprises the totality of this population for the PA. These pilots are divided into two classes, and they share common aircrafts, specifically the Aerospatiale Epsilon TB-30. Additionally, both classes are assigned comparable workloads and operational tasks.

Within these criteria there are 19 individuals serving as military pilots actively engaged in their training (tirocinium) at the PAA, specifically within the PA course titled “Masters in Military Aeronautics: Aviator Pilot Specialist,” and our sample size is calculated with OpenEpi, with a 95% confidence interval, which corresponds to 19 subjects—the totality of this population, as seen in Image 1.

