**IMAGE 1 fig1:**
[figure not shown]
Sample size for frequency in the military pilot’s population using OpenEpi.

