#### Statistical analysis

3.3.4

Sample size was calculated with OpenEpi. Data analyses will be done with MATLAB (18) and Jamovi (29), based on the type of data; analyses will be performed based on the underlying assumptions for parametric, or non-parametric testing. In detail, for all difference testing, data and variance distribution (i.e., normality) will be checked. The alpha-error threshold is set at 5%, all *p* values below are considered significant.

For the primary outcomes related with postural control and heart rate variability a MATLAB (18) routine will be used to treat data exported from the Biosignals Plux platform and also from the Polar H10 portable monitor, and with those values a Shapiro–Wilk normality test will be performed and either a T-test for paired samples will be applied on parametric data or a Wilcoxon rank test will be applied on non-parametric data.

For the primary outcomes related with operative performance and the secondary outcomes a Shapiro–Wilk normality test will be performed and either a T-test for paired samples will be applied on parametric data or a Wilcoxon rank test will be applied on non-parametric data.

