## Results

4

The principal objective of the study is to assess the feasibility and efficacy of implementing a 12-week yoga program to enhance existing military training protocols within the Portuguese Air Force. This will be accomplished through the utilization of a randomized controlled intervention design. The intervention comprises preventive exercises tailored to address perceived challenges faced by pilots during aircraft piloting, thereby enhancing the capabilities of individuals who are already undergoing training.

The findings of this study hold significance for the research group and are equally pertinent for policymakers within the Portuguese Air Force. The data gathered in this project can aid policy makers in developing a tailored exercise regimen.

Broadening the study’s relevance to diverse contexts, the methods, results, and discussions generated by this project have the potential to be extrapolated to diverse military contexts, beyond military aviation, exploring applications of human intervention in different military settings, such as incorporating new training techniques for: airfield operations officers, paratroopers, armored vehicle operators, tank crews, navy divers, military paratroopers, and others, where the improvement of physical and cognitive abilities aligns with the outcomes of this study. Furthermore, the applicability of the project’s findings extends to high-demand environments beyond military, including civil aviation (both for pilots and air traffic controllers), professional race car or motorcycle drivers and skydiving companies—professions where the optimization of physical and cognitive capabilities may offer valuable insights and benefits.

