## Discussion

5

Recognizing the critical role of cognitive performance in military operations, where impaired cognitive function is a prominent factor in accidents during training and combat (30), instructors must prioritize not only the physical health but also the psychological well-being of trainee pilots (31). The potential to enhance sensory systems, particularly through vestibular habituation and adaptation, can influence sensory weighting and postural behavior, the processing of sensations, along with their identification and integration with others, providing a comprehensive framework of possibilities for decision-making and action planning (32). Consistent yoga practice contributes to ongoing improvement in postural control, muscle strength, and the vestibular system, fostering increased plasticity in the sacculocolic pathway and resulting in enhanced vestibular evoked myogenic potential (cVEMP) responses (32). Furthermore, Ashtanga Yoga, in accordance with Patanjali, encompasses techniques that address all facets of the human system, including the body, breath, mind, personality, and emotions (11).

A notable strength of this intervention lies in its practicality and cost-effectiveness. Furthermore, all exercises are executable without the need for additional materials and can be conducted in spaces already designated for training, such as a gym room or outdoors when weather conditions permit.

The sample size may present challenges in interpreting results and deducing the practical relevance of the study. Challenges in maintaining blinding among pilots also present potential limitations. These are mitigated by including the totality of this population, designating the control group as a waiting list, offering them the same intervention subsequently, and ensuring blinding for all investigators except the study coordinator.

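### The stated basis for 19 subjects is a formula for estimating one frequency in a finite population, which says nothing about detecting a difference between two arms

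*Protocol article*

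**What the plan says.** Under Sample size determination (3.2.1), the article identifies the eligible population: "There are currently 19 pilots actively undergoing their training (tirocinium) at the PAA". It then states that "our sample size is calculated with OpenEpi, with a 95% confidence interval, which corresponds to 19 subjects", and adds that this is everyone in that population. The calculation is shown in Image 1. The image is not reproduced in the text at hand, but its caption reads "Sample size for frequency in the military pilot’s population using OpenEpi". Statistical analysis (3.3.4) repeats "Sample size was calculated with OpenEpi" and sets alpha at 5%. These sections give no power, effect size, SD or allocation ratio.

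The study is described in 3.1 in these terms: "A randomized, prospective, controlled two-arm trial will be adopted". The Results section gives the principal objective as to "assess the feasibility and efficacy of implementing a 12-week yoga program". The primary and secondary outcomes (2.1 and 2.2) are changes from baseline to 12 weeks in quantities such as task times, error counts, heart rate variability, centre of pressure, grip strength and questionnaire scores.

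The Discussion concedes that the sample size may make the results and their practical relevance hard to interpret. It names blinding of the pilots as a second limitation, and continues: "These are mitigated by including the totality of this population". The waiting-list design and blinding of investigators are listed in the same sentence as further mitigation.

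**The concern.** The caption names a survey calculation: how many people to sample from a known finite population so that one proportion is estimated to a chosen margin. This trial asks whether two randomised groups differ in how they change, and none of its listed outcomes is the prevalence of something among pilots. The calculation therefore answers a question that the trial does not ask.

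It also cannot warn of a problem. The finite-population correction caps the answer at the population size, so the routine can never report that 19 is too few. A reader who sees a sample size calculated at 95% confidence may take it as support for the efficacy comparison, which it is not.

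The mitigation sentence adds to this. Taking everyone removes sampling error when a frequency in those 19 people is being described. It does not remove the chance imbalance that comes from dividing them at random into two groups of about 9 and 10. The article directs its findings to Air Force policy makers and hopes to extend them to other military and civil settings, so its readers need to know how little the between-arm contrast can resolve.

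**Working it through.** **Reproducing the stated figure.** Inputs from the article: population N = 19; confidence 95%, so z = 1.96. The expected frequency p and margin d would be in Image 1, which is not visible. I assume p = 50% and d = 5 points, with no design effect.

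n = N p(1 − p) / [(d²/z²)(N − 1) + p(1 − p)]

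= 19 × 0.25 / [(0.0025/3.8416) × 18 + 0.25]

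= 4.75 / 0.2617 = 18.15, rounded up to 19. The stated figure is reproduced.

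**Sensitivity to the unseen inputs.**

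| p | d (points) | n before rounding up |
|---|---|---|
| 50% | 3 | 18.7 |
| 50% | 5 | 18.15 |
| 50% | 10 | 16.0 |
| 30% | 5 | 18.0 |
| 10% | 5 | 16.8 |
| 10% | 10 | 12.5 |

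At p = 50% and d = 5 points, confidence levels from 80% to 99.99% give 18 or 19 after rounding. The answer is not 19 for every p and d. But as d shrinks to zero the first term of the denominator vanishes and n tends to N, so n cannot exceed 19. No feature of the trial design enters the formula.

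**What 19 pilots give as a two-arm comparison.** Assumptions: all 19 complete; split 9/10 (no ratio is stated); two-sided 5% (sidedness is not stated); a two-sample t comparison. Degrees of freedom are 17 and the noncentrality is δ√(9 × 10/19) = 2.176δ, where δ is the difference in SD units.

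| True difference (SD) | Power |
|---|---|
| 0.5 | 18% |
| 0.8 | 38% |
| 1.0 | 54% |
| 1.2 | 69% |

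Solving for power gives a detectable difference of 1.37 SD at 80% and 1.58 SD at 90%. As a check at 80%, the normal approximation is (1.960 + 0.842) × √(1/9 + 1/10) = 2.802 × 0.4595 = 1.29 SD, a little lower as expected with so few degrees of freedom.

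**Sensitivity of the 1.37 SD.** An uneven split of all 19 hardly matters: 1.38 SD at 8/11 and 1.41 SD at 7/12. Loss of pilots matters more: 1.46 SD with 8/9 completing and 1.57 SD with 7/8. With an analysis adjusted for baseline, and an assumed baseline-to-12-week correlation of 0.5 to 0.7, the 9/10 figure would fall to about 1.2 to 1.0 SD. The article names paired t or Wilcoxon tests and not that analysis, so those lower figures do not describe the trial as written.

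**The case against.** The strongest reply is that the number was never really a statistical choice. The article says that these 19 are all the eligible trainees, and the Discussion explains that security and operational limits put other pilots out of reach. No calculation could have changed enrolment. This stands: enrolling all 19 is a sound choice, and it would be wrong to infer that the trial must recruit more or should not run.

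It is also true that the arithmetic reproduces, that the Discussion openly names sample size as a limitation, and that the article nowhere claims adequate power. The mitigation sentence covers two limitations and several measures together, and it says mitigated, not removed. Taking everyone does maximise the attainable number and avoids selection among current trainees, which bears on the practical relevance that the Discussion mentions. A reader might infer that the authors believe a census abolishes random error in the comparison, or that they will take a non-significant result as proof of no effect. The text says neither.

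It might further be said that Image 1 cannot be seen, or that a fuller plan covers the matter. The caption identifies the method, and the conclusion holds for any p and d. Nor is this an omission: the article itself states a calculation and offers it as the basis of the sample size. What remains is that the basis offered is the wrong kind, and that the concession about size is softened by an argument that does not reach the between-arm contrast.

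**Conclusion.** The concern holds as a fault in the stated rationale. A precision formula for one frequency is presented as the sample size of a randomised efficacy comparison; it mostly restates the population of 19 and carries no information about a difference between arms. The claim that full enrolment mitigates the small size does not hold for the precision of that difference.

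The figure of 1.37 SD is close to a best case for an unadjusted comparison, because it rests on full participation and completion and a near-even split. At a true difference of 0.5 SD, such a comparison would miss the effect about four times in five (100% − 18% = 82%). The documents give no SD, target effect or power, so no corrected sample size can be derived, and none is needed, since the number is set by availability.

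**What to change.** Change the wording in four places:

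1. In 3.2.1 and 3.3.4, remove the OpenEpi frequency calculation and Image 1 as the justification. State that the sample size of 19 is fixed by the trainees available and that no power-based calculation was made.
2. Give the detectable between-arm difference with its assumptions: about 1.37 SD at 80% power and two-sided 5% if all 19 complete and are split 9/10, rising to about 1.46 to 1.57 SD with 8/9 or 7/8 completing. Add that power is about 18% at 0.5 SD and 38% at 0.8 SD.
3. In the Discussion, keep the point that full enrolment maximises the attainable number and avoids selection among current trainees. Add that it does not reduce the imprecision of the between-arm comparison, so a non-significant result is not evidence of no effect.
4. Quote the figures of about 1.0 to 1.2 SD (assumed correlation 0.7 to 0.5), and commit to reading results from the confidence interval of the between-arm difference, only if the analysis is changed to a baseline-adjusted comparison between arms.

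The cost is text only. No extra pilots are needed, and items 1 to 3 leave allocation, outcomes and tests as they are. The downside is that the stated justification becomes less favourable.
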